#### Parental leave eligibility and compensation

In Sweden, all legally residing parents are eligible to receive parental leave benefits (ie, job-protected leave), including biological parents as well as individuals with child custody.^10^ Individuals must apply for these benefits through the Social Insurance Agency, the governmental authority that decides on and administers insurance and contributions to families and children in Sweden.^11^ The benefits are split into general flat-rate or earnings based benefits, collectively referred to as ‘parental benefits’ and applied to 390 out of the total 480 days, while the remaining 90 days are paid at a second flat rate, henceforth referred to as ‘guarantee days’.^7^

To be eligible for earnings based parental benefits, an individual must have been employed for at least 240 consecutive days prior to the estimated delivery date with a minimum annual income of 82 100 Swedish kronor (SEK) (in 2020). Although the remuneration level has varied over time, individuals today receive approximately 80% of their salary up to a certain ceiling (1006 SEK per day in 2020) from the Social Insurance Agency, with potential top-ups from the employer.^12^ If an individual has an income below a certain level (117 590 SEK in 2020) during the 240 days before childbirth, they are only entitled to a general flat-rate benefit (250 SEK per day in 2020) for the first 180 days which they claim for the child. After 180 claimed days, parents can receive benefits based on their current earnings.^7^ Finally, if an individual has no income or an annual income below the stipulated level throughout the leave period, they will receive the general flat-rate benefit for the full 390 days. However, if an individual is sick, a student or unemployed but a ‘job seeker’, they can receive parental leave benefits based on their prior income if they have registered with the Public Employment Service.^10^ Regardless of employment history, the final 90 days are always paid at a minimum guaranteed level of 60 SEK starting in 1987 and 180 SEK since 2006.^7^

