#### Policy reforms

The Swedish parental leave system has undergone several reforms over the past half-century. We define a ‘policy reform’ as any change implemented at a specific time that could impact either uptake or sharing of parental leave, as well as eligibility for earnings based benefits. To evaluate the unforeseen health consequences of the parental leave policy—that is, a welfare policy that does not primarily target health—we will concentrate on reforms that have either been shown to accomplish their primary aim (ie, the speed premium, father’s quota and double days reforms) or with undoubtedly significant, although unintended, impacts (ie, the doubled value of general flat-rate benefits).

Doubled flat-rate benefits: Although not explicitly a reform, the doubling of the general flat-rate benefits from 60 SEK per day (from 1987) to 120 SEK per day (in 2002) aimed to secure the economic welfare of low-income families.

Speed premium: Since earnings related parental leave benefits are estimated based on one’s salary prior to childbearing (at approximately 80% of the salary), parents having children in quick succession may choose to temporarily reduce their working hours or be unable to return to work at all and will thus have lower benefits for their second and subsequent births. In 1980, a supplement (commonly referred to as the ‘speed premium’) was introduced to safeguard women’s income between parental leave periods, ensuring that for births with up to 24 months’ spacing^13^ and then with up to 30 months’ spacing (following a 1986 expansion),^14^ all earnings based benefits could be based on the parents’ salaries prior to the birth of their previous child, if higher than their current income. An evaluation of the 1986 expansion revealed that an increased proportion of Swedish-born parents had children in short succession; even if this was an unintended consequence, the reform has henceforth been called the ‘speed premium’.^14^

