### Covariates

Annual information on parental leave uptake (number of days) for each parent will also be available from LISA. Specific information on parental leave eligibility and uptake (including length of paid and unpaid leave) will be retrieved from the SIAD.

Demographic characteristics will include parents’ age at childbirth, country of birth (ie, Swedish vs other and specific origins) and marital and cohabitation status, from the TPR and LISA. Sociodemographic characteristics including educational attainment, household disposable income, individual labour income, employment status and receipt of sick leave benefits will be drawn from LISA.

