### Study design and statistical analyses

A variety of advanced designs and statistical methods for observational data will be applied. First, using descriptive and correlational designs, we will implement standard multivariable methods to quantify links between prebirth health conditions, parental leave eligibility and uptake, and postbirth health outcomes while accounting for confounding using relevant covariates and heterogeneity analyses.

Second, we will use robust quasi-experimental approaches to assess the causal effects of parental leave policy on health, reducing the risk of selection effects and unmeasured confounding by harnessing the natural, ‘as-if’ randomisation around policies.^45 46^ With this approach, we can isolate the absolute policy effects on health even in the absence of detailed information on changes in parental leave uptake. These approaches include interrupted time series (ITS), regression discontinuity (RD) and difference-in-difference (DiD) designs. For ITS designs, segmented regression models will be adjusted for seasonality and trend while accounting for autocorrelation.^46^ For RD designs, continuity around the cut-off will be tested using the McCrary Density Test and similarity of eligible and ineligible observations will be determined through descriptive statistics. Finally, for DiD designs, we will examine the data to confirm parallel trends and other relevant assumptions.^45^

RQ#1: We will examine the effects of the 2002 doubling of flat-rate benefits on the mental health of parents. An RD design will be applied to plot psychiatric hospitalisation rates with labour income as a forcing variable, with separate plots before (with an income cut-off equivalent to 75 SEK, at 80% reimbursement rate) and after 2002 (with a cut-off equivalent to 150 SEK daily). Cut-offs for both parents’ income will be examined. We will triangulate our findings with a DiD approach, comparing those eligible for the increased benefits to those ineligible before and after reforms.

RQ#2: A segmented-regression ITS of monthly birth data comparing the rate of low birth weight and preterm births 3 years before and after the 1980 and 1986 speed premium reforms will be implemented. We will also compare the prevalence of obesity in mothers early in their second pregnancy before and after the reform.

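### RQ#1 sets one open-ended 150 SEK cut-off after 2002 that is right only while the flat rate is 120 SEK, and its income variable is only a proxy for benefit status

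*Protocol article*

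**What the plan says.** Under Study design and statistical analyses, RQ#1 plots psychiatric hospitalisation rates against labour income as the forcing variable. There are two plots: one before 2002, "with an income cut-off equivalent to 75 SEK, at 80% reimbursement rate", and one later, "and after 2002 (with a cut-off equivalent to 150 SEK daily". A difference-in-difference (DiD) comparison of eligible and ineligible parents is planned as triangulation. No birth-year window is given for either RQ#1 analysis.

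Policy reforms describes the change being studied as the "doubling of the general flat-rate benefits from 60 SEK per day (from 1987) to 120 SEK per day (in 2002"). Parental leave eligibility and compensation says that, below an income level, parents face the position that "they are only entitled to a general flat-rate benefit (250 SEK per day in 2020"). The income level is 117 590 "SEK in 2020) during the 240 days before childbirth". The same section requires that a parent be "employed for at least 240 consecutive days prior to the estimated delivery date" and lets sick people, students and registered job seekers be paid on earlier income.

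Covariates draws individual labour income from LISA, and also states: "Specific information on parental leave eligibility and uptake (including length of paid and unpaid leave) will be retrieved from the SIAD". Additional analyses names annual labour income as the means of determining eligibility in subgroups. Study population covers first births from 1973 to 2019.

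**The concern.** An RD estimates an effect only if treatment changes at the point where the analysis looks for a break. Two features of RQ#1 put that in doubt.

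First, the post-reform threshold is a single number with no end date, although the protocol itself shows that the flat rate had more than doubled again by 2020. Once the rate exceeds 120 SEK, parents just below and just above 150 SEK/day all receive the same flat-rate benefit. A comparison at 150 then contrasts groups treated alike, and pooling such births with earlier ones dilutes any true effect. The planned density test and the check of similarity across the cut-off would not reveal this, because they too would be run at the wrong point.

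Second, the only income basis described for eligibility is annual, whereas the benefit is assigned on a different period and with exceptions. Some parents on each side of the income threshold will have the other side's benefit. Analysed as though crossing the threshold settled benefit status, this also shrinks any estimated break. A null RQ#1 result could then be read as evidence that the benefit level does not matter for mental health, when the design could not have shown otherwise.

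**Working it through.** **Inputs.** Flat rates of 60 SEK (from 1987) and 120 SEK (2002): Policy reforms. Cut-offs of 75 and 150 SEK/day and the 80% rate: Study design and statistical analyses. Flat rate of 250 SEK and thresholds of 117 590 and 82 100 SEK, all for 2020: Parental leave eligibility and compensation.

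**Step 1: reproduce the plan's cut-offs.** The cut-off is the income at which 80% of earnings equals the flat rate, i.e. flat rate / 0.80.
- Before 2002: 60/0.80 = 75 SEK/day.
- From 2002: 120/0.80 = 150 SEK/day.

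Both agree exactly, so 150 is tied to the 120 SEK rate.

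**Step 2: apply the same formula to the 2020 rate.**
- 250/0.80 = 312.5 SEK/day.
- From the stated threshold: 117 590/365 = 322.2 SEK/day. The implied replacement is 250/322.2 = 77.6%, consistent with the protocol's approximate 80%.
- Ratio to the fixed cut-off: 312.5/150 = 2.08 and 322.2/150 = 2.15.
- Distance from it: 312.5 − 150 = 162.5 and 322.2 − 150 = 172.2 SEK/day.
- The lower annual minimum of 82 100 SEK, which is a separate condition, gives 82 100/365 = 224.9 SEK/day and is also above 150.

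**Step 3: what happens at 150 SEK/day.** Take the benefit as the larger of the flat rate and 80% of income, and compare parents at 140 and 160 SEK/day (80% gives 112 and 128).
- Flat rate 120: they receive 120 and 128. The schedule bends at 150, as intended.
- Flat rate 250: both receive 250. Nothing changes at 150.

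**Step 4: range of the error.** The protocol does not say when the rate rose between 2002 and 2020, so no cut-off can be computed for the years between. The error is 0 for births while 120 SEK applied and at most about 172 SEK/day at the 2020 level. That year lies just outside the 1973–2019 population.

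**Step 5: the income variable against the rule.**
- Rule: income in the 240 days before birth, with earlier income allowed for sick people, students and registered job seekers.
- Plan: labour income from LISA, described as annual where eligibility is mentioned; RQ#1 gives no reference period.

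Annual income covers a different span from the rule and does not capture the exceptions. Crossing the threshold therefore changes the probability of flat-rate status without determining it, which is the definition of a fuzzy design. If income in the year of birth were used, leave-taking would itself lower it.

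**The case against.** The strongest reply is that RQ#1 concerns the 2002 doubling, and for that contrast both cut-offs are exactly right. The 1973–2019 span is the umbrella for five research questions; RQ#2 uses 3 years on either side of its reforms, and a similar window here might give no error at all. A journal article may leave the window to a fuller plan.

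Much of this stands. A reader might infer that the protocol applies 150 SEK to every year up to 2019; it does not say so. The 2020 figures are an out-of-period bound and do not show an error for any particular study year. But the article does commit to a number and an unbounded period, and Limitations promises long follow-up in years since each reform. A restriction that makes the number correct has to be stated.

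For the income variable, a reader might infer that calendar-year income is fixed as the forcing variable. It is not: that follows only from LISA and from the subgroup text, and the eligibility rule is itself partly in annual terms. Nor can misclassification be read off day counts. If preceding-year income were used, it would share on average 79 of the 240 qualifying days (33%, with births spread evenly over the year), but a parent with steady pay is classified correctly even with no overlap.

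A reader might also infer that the DiD groups are formed with the same 150 SEK cut-off. The protocol says only that eligible and ineligible parents are compared, so that charge is unsupported. Finally, the SIAD is said to hold eligibility and uptake; nothing shows that it holds the qualifying income.

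**Conclusion.** The point holds in a bounded form and should be settled before RQ#1 is analysed. The 150 SEK/day cut-off is correct while the flat rate is 120 SEK and wrong for any births included after the rate rose. The error runs from 0 to about 172 SEK/day, the upper end resting on 2020 figures, and its direction is towards hiding any break. How much of it enters the analysis depends on the birth-year window and the dates of the rate rises, neither of which is stated.

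Separately, income as described is a proxy for the rule that assigns the benefit, so the RD is fuzzy, not sharp. The share of parents misclassified cannot be derived from the protocol.

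**What to change.** 1. State the birth-year window for the RQ#1 RD.
2. Either restrict the later plot to births while the 120 SEK rate applied, or set the cut-off for each year as the flat rate divided by the replacement rate in force, and pool years on income centred at that cut-off.
3. Define the running variable as income measured before birth, not income in the year of birth.
4. Analyse as a fuzzy RD: income is the running variable, and actual flat-rate versus earnings-based status from the SIAD is the treatment modelled in the first stage. Confirm first that the SIAD data separate these two statuses.
5. Use SIAD status, rather than the income cut-off, to check the DiD eligibility groups.

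The cost is a small table of yearly rates and use of a register already in the plan. The statistical price is precision: a fuzzy RD estimate is less precise than a sharp one, and restricting to the 120 SEK years leaves fewer births.

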#### Length and flexibility of parental leave

Sweden has developed into one of the most generous and flexible paid parental leave systems worldwide.^6^ Starting in 1974, parents were entitled to 6 months of leave to be used within 270 days of birth and shared by the parents as they desired. An additional 9 months of leave were introduced incrementally from 1975 to 1989,^6 7^ with an extension to use a portion of the leave until the child turned 8 years old in 1978. In 1995, 1 month of the leave was reserved for each parent, a quota which was further extended by 1 month each in 2002 and 2016.^8 9^ Since 2014, couples have been entitled to use 480 parental leave days up until the child turns 12 years old. Of these days, no more than 96 can be used after the child’s fourth birthday.^7^

We will focus on mothers’ and fathers’ paid parental leave (ie, job-protected leave paid at set benefit levels) rather than unpaid parental leave (ie, job-protected unpaid leave in the first 18 months after birth). Furthermore, we do not examine maternity leave (ie, 2 weeks of mandatory job-protected leave for the mother prior to or after childbirth, which can be unpaid or paid as standard parental leave days), temporary leave, including at birth/adoption (formerly paternity leave; ie, up to 10 days of separate paid, job-protected leave for partners to attend the delivery or assist the mother with infant care) or leave for the care of sick children.^6 7^

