Father’s quota: Fathers have been eligible to use parental leave since 1974, when parents could choose to divide parental leave days between themselves as they saw fit. However, most days were transferred to and claimed by mothers, with an average use of 320 days in 1994, reinforcing mothers’ ‘double burden’ of childcare and work. In response, a father’s quota reform was implemented in 1995, reserving a month of leave exclusively for the father, to be forfeited completely if left unused (similarly, a 30-day reserve was allocated to the mother, ie, a mother’s quota). It succeeded in increasing the proportion of fathers using parental leave from 43% to 75%.^15^ The father's quota was expanded to 2 and 3 months in 2002 and 2016, respectively, but with smaller impacts on uptake.^6^

Double days: In 2012, 30 days of existing parental leave were designated as ‘shareable’, that is, could be used simultaneously by both parents within the child’s first year of life. By granting flexibility to the couple in their leave use, this ‘double days’ reform aimed to facilitate the transfer of care from one parent to another. In fact, the reform significantly increased the proportion and number of father’s leave days used in the first half-year after childbirth.^16^

All reforms were implemented nationally on 1 January of the indicated year.

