The father’s quota was implemented to promote a gender-equitable work-life balance and shared parenting. However, the health consequences of the father’s quota have been debated, with a lack of empirical evidence on its differing mechanisms. Studies have shown a positive association between the father’s parental leave use and healthy behaviours, including decreased alcohol use and increased physical activity,^22 23^ as well as decreased mortality risks.^24^ Nonetheless, there may be situations in which fathers’ leave use is less optimal for or even unfavourable for the family. The quota may have encouraged mothers to return to work sooner, potentially interrupting their physical and psychological recovery from pregnancy and childbirth. These potential adverse effects among parents could extend to the child: shorter maternity leave in the child’s first months could shorten breast feeding, a risk factor for childhood obesity^25^ and respiratory track infectious in the first 2 years of life.^26^ However, there is a lack of evidence on changes in mothers’ labour supply following the reform,^27 28^ suggesting that mothers may have stayed at home with fathers on an unpaid basis, foregoing their income and thus potentially creating psychological strain, especially among low-income parents.

Given that parental leave in Sweden is longer than in most other contexts, it can be argued that any health effect of shortened parental leave among mothers with the introduction of the father’s quota would be negligible. However, adverse effects may become apparent in specific subpopulations, including for couples only entitled to flat-rate benefits (that may therefore need to return to work early), as well as individuals with job insecurity or who are self-employed. Identifying adverse health effects in population subgroups will not only shed light on the differential impacts of parental leave reforms within a population but also will have implications for policy transferability in international contexts where parental leave is generally shorter and discussions on reserved days for the father are ongoing.

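### The RQ#1 difference-in-differences cannot separate the 2002 flat-rate doubling from any difference between flat-rate and earnings-based families in the effect of the second father's-quota month introduced at the same time

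*Protocol article*

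**What the plan says.** Under Study design and statistical analyses, RQ#1 studies the 2002 doubling of flat-rate benefits and parents' mental health. A regression discontinuity (RD) in labour income comes first, with separate plots before and after 2002. The difference-in-differences (DiD) follows as support: "We will triangulate our findings with a DiD approach, comparing those eligible for the increased benefits to those ineligible before and after reforms".

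Three statements on timing matter:

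- Policy reforms puts the rise from 60 to 120 SEK per day in 2002. It introduces the change with the words "Although not explicitly a reform, the doubling of the general flat-rate benefits", but lists it among the reforms to be studied.
- The same section says that the father's "quota was expanded to 2 and 3 months in 2002 and 2016, respectively, but with smaller impacts on uptake". Length and flexibility of parental leave agrees: "a quota which was further extended by 1 month each in 2002 and 2016".
- Policy reforms closes with "All reforms were implemented nationally on 1 January of the indicated year".

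On who might be harmed by the quota, Unintended health consequences of the Swedish parental leave system says that "adverse effects may become apparent in specific subpopulations, including for couples only entitled to flat-rate benefits".

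For DiD designs the article promises a check of parallel trends and of other assumptions that it does not name. Neither RQ#1 nor Limitations mentions that two policy changes fall in 2002.

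**The concern.** A before/after-2002 contrast between parents eligible and ineligible for the higher flat rate measures everything that changed differently for the two groups in 2002. The benefit level is one such change. The second quota month is another if its health effect differs by income group.

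The article points to such a difference, and in an awkward direction. It expects the doubled benefit to help low-income families, and it suggests that reserved days may harm couples who have only flat-rate benefits. If both are true, the two effects pull against each other in the same group. A real benefit could be diluted or hidden, or a quota effect could be credited to benefit level. RQ#1 is framed as a question about benefits, and the article says that its quasi-experimental designs can isolate policy effects, so a joint effect could be reported as a benefit effect.

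**Working it through.** **Do the changes coincide?** Both are dated 2002. The closing sentence of Policy reforms gives 1 January. Because the doubling is described as not strictly a reform, its exact day is the natural reading and not a certainty. This makes no difference here: a contrast split at 2002 contains both changes.

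**What does the DiD estimate?** Let b be the benefit effect in the eligible (flat-rate) group, qF the effect of the second quota month in that group, qE its effect in the ineligible (earnings-based) group, and t the time change common to both.

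- Change in the eligible group: b + qF + t
- Change in the ineligible group: qE + t
- DiD = (b + qF + t) − (qE + t) = b + (qF − qE)

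The estimate is unbiased for b only if qF = qE.

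**How large could the bias be?** The documents give no rates or effect sizes. The values below are assumptions, in psychiatric admissions per 1000, and only show how the formula behaves.

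| b | qF | qE | qF − qE | DiD |
|---|---|---|---|---|
| 0 | +1.0 | +1.0 | 0 | 0 |
| 0 | +1.0 | +0.5 | +0.5 | +0.5 |
| 0 | +1.0 | 0 | +1.0 | +1.0 |
| −0.5 | +0.5 | +0.5 | 0 | −0.5 |
| −0.5 | +0.5 | +0.25 | +0.25 | −0.25 |
| −0.5 | +0.5 | 0 | +0.5 | 0 |

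Full cancellation (last row) needs a differential quota effect equal and opposite to b. Smaller differentials only dilute the estimate.

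**Do the stated checks separate the two changes?**

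- Parallel trends are judged on data from before 2002 and cannot reveal a second change in 2002 itself.
- Multiple intervention points (Additional analyses) are specified for interrupted time series only.
- Pseudo-intervention dates test other dates. Prebirth outcomes precede exposure to the quota.
- Income subgroups do not help within this DiD, because income already defines its groups.
- Limitations treats outside influences as changes in population composition and does not name this overlap.

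**Is the RD exposed in the same way?** The stated cut-offs reproduce: 60/0.80 = 75 SEK and 120/0.80 = 150 SEK per day. Within either period the same quota rule applies on both sides of the cut-off, so the quota does not create a contrast there. Two cautions apply. Since 0.80 × 75 = 60 and 0.80 × 150 = 120, the earnings-based payment equals the flat rate at the cut-off, so the benefit changes slope there and does not jump. And comparing the pre-2002 plot with the post-2002 plot could bring back a quota effect that varies with income.

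**The case against.** The best defence has four parts.

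*The quota was national.* A reader might infer that the DiD credits to benefit level everything the quota did to flat-rate families. It does not. The comparison group received the same month, so the shared part cancels and only qF − qE remains. This objection stands.

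*The article does not say that the effects differ.* A reader might infer that the plan's own reasoning shows the equal-effect assumption to fail. The text says only that effects may appear. It discusses the quota's introduction, not the 2002 expansion, and it also names people with insecure jobs and the self-employed. Its unit is the couple, while RQ#1 examines each parent's income. The assumption is therefore open to question but not refuted. The article also reports smaller uptake effects for the later expansions, which may limit the bias without making it zero.

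*The DiD is supporting evidence.* The RD is listed first and is less exposed. That lowers the severity. It does not remove the problem, because an analysis meant to corroborate the RD should estimate the same quantity.

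*Existing plans could help.* Income subgroups are to be considered for all research questions, and applied to the 1995 analysis they would show quota effects by benefit status. That is useful, but the article does not link it to the 2002 DiD.

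A reader might also infer the reverse problem for RQ#3, since that question mentions the quota's expansion. The analysis described for RQ#3 uses 1995 only, and Limitations says that the first reserved month is the main focus. No 2002 quota analysis is planned, so that inference is not supported.

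**Conclusion.** The point holds in limited form. As planned, the RQ#1 DiD estimates b + (qF − qE), and nothing stated separates the terms. The bias is the difference in quota effect between the two groups. Its size cannot be derived from the documents: it is zero if the second month affected both groups alike, and it reaches the whole of qF only if earnings-based families were unaffected.

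The conclusion rests on two things: both changes belonging to the same before/after split, which the stated years establish, and a differential quota effect being plausible, which the article suggests but does not show. The consequence is for what the DiD may be said to show. RQ#1 does not fail as a whole, because the within-period income cut-off analysis does not share this weakness.

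**What to change.** In Study design and statistical analyses, RQ#1:

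1. Keep the within-period income cut-off analysis as the main analysis, with the reason that the quota rule is the same on both sides of the cut-off.
2. State that the 2002 DiD estimates the joint effect of the flat-rate doubling and any differential effect of the second quota month, unless that differential can be shown to be small.
3. Run the same income-group DiD at the 1995 quota introduction as a benchmark for qF − qE. The article gives 60 SEK from 1987 until the 2002 doubling, so it lists no flat-rate change at 1995. The LISA register starts in 1990, so labour income is available for the years just before. The benchmark is imperfect: fathers' use rose from 43% to 75%, a larger response than in 2002, and the article itself warns of the 1990s economic crisis.
4. Add 2016 only if no flat-rate change coincides and follow-up allows. The flat rate went from 120 SEK in 2002 to 250 SEK in 2020 in steps that the article does not date. If data end in 2019, 36 months of follow-up exist only for births through 2016 (2019 − 3), about one year after the change.

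In Limitations, name the 2002 overlap.

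The cost is one or two additional runs of a planned model, a check of the flat-rate dates, and a narrower DiD conclusion.
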